### Exclusion Criteria

The following exclusion criteria will apply:

Patients with peritoneal metastases.Patients with ASA physical status IV-V.Emergency surgery: that is required to deal with an acute threat to life.Inability to give written informed consent.Surgery for recurrent disease of the included procedure.Palliative surgery: performed only for symptom relief even despite negligible impact on the patient's survival.

## Quality Control

### Center Registration

Centers will be allowed to upload data after the registration procedure. Local ethics committee approval is needed, and each study local lead will be responsible for local study approval before the study start. Each center will register a principal investigator and a co-investigator for each type of procedure eligible for the study.

### Surgeon Registration

Invitation emails will be sent to every associated member by the AEC. Data about hospital characteristics (academic, teaching, referral, or country hospital, number of beds) and surgical volumes both for robotic and laparoscopic surgery will be registered using a Google Form survey (Google, Mountain View, California, USA): https://forms.gle/eHCELgr5nZCRwUgP9. Each surgeon introducing data and participating in the study will be asked about his previous experience in both laparoscopic and robotics concerning the selected procedure.

## Data Collection

### Clinical Data

Clinicians will be requested to register medical data related to surgery (operation equipment, skin-to-skin operating time, blood loss, surgical equipment, number of surgeons), hospital stay (intensive care unit, high dependency unit, ward), complications and associated management (interventions, additional imaging, additional hospitalization). This data will be entered into an electronic Case Report Form (eCRF) online database (CASTOR).

Complications will be classified according to the Clavien-Dindo classification of surgical complications (26) and registered as adverse or serious adverse events. Participants' overall morbidity will be assessed using the Comprehensive Complication Index (CCI) (27). The 95% confidence intervals (CI) for the difference in the means between the two groups will be reported as a primary result. Since the CCI is approximately normally distributed, the 95% CI can be computed using the normal distribution. Further descriptive measures will be reported in terms of mean and standard deviation.

Missing data will thus be managed depending on the cause of missingness. If missingness may directly or indirectly be related to the treatment, it may cause a bias even in the intention-to-treat analysis. In such a situation, the missing data will be reported in the final report, and missing data in the intention to treat analysis will be analyzed according to the worst-case scenario method (failure).

## Data Completeness

### Questionnaires

All participants will be asked to provide an additional informed consent to receive the validated QoL questionnaires EuroQol EQ-5D-5LTM (official Spanish version) and will be asked to score five aspects of health status using the EQ-5D™ questionnaire: mobility, self-care, usual activities, pain/complaints, and mood (anxiety/depression). This questionnaire is considered the most representative QoL tool for cost-effectiveness studies (28). Patients will receive questionnaires at inclusion, one, and 3 months after surgery, by mail, digitally, or in person, according to their preference.

### Cost Data

Data on costs will be collected from the Spanish Hospital Costs Network (*Red Española de Costes Hospitalarios, RECH*
https://www.rechosp.org/rech/faces/en/jsf/index.jsp). RECH is an official Spanish project initiated to obtain an extensive database to provide reliable information on the per-patient cost of hospital care. The RECH database is a healthcare database that brings together the results of different management efforts in many Spanish Healthcare System institutions. Overall direct hospital costs will be collected, except for the costs associated with the acquisition or maintenance of the robotic device. Pre-admission charges for screening will not be considered, as these are equal for both surgical techniques. All readmission-related costs will be added to the total hospital expenses. A discount rate of 3% per year will be used to estimate the costs and QALYs, as recommended by health economic guidelines (28). All costs will be presented in Euros (exchange rate 2022).

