## Current Evidence

Several studies have shown that robotic-assisted surgery is associated with higher costs than laparoscopy (6–8). Contributing factors include purchasing the robot by the healthcare institution, maintenance costs, disposable materials, and longer operative times. These apply to most general surgery procedures; but some organ- and procedure-specific considerations are needed.

Regarding distal pancreatectomy, two recent meta-analyses aiming to compare the costs of robotic and laparoscopic distal pancreatectomy, demonstrated that the latter seems to contain costs, despite some potential technical advantages of the robotic technique (e.g., decreased conversion rate) (8, 9). However, the surplus cost of robotic distal pancreatectomy resection might be reduced given the decrease in hospitalization costs.

Regarding rectal surgery, six studies in the literature reported on the costs of robotic vs. laparoscopic rectal resection (7, 10–14). According to Morelli et al., hospital costs were slightly higher in the laparoscopic group, whereas higher operative costs were reported in the robotic rectal resection group (11). Baek et al. reported overall costs to be higher in the robotic group, and data on hospitalization costs were found to be generally lacking (13).

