Some published result must be interpreted with caution as the analysis is based on heterogeneous data with outcomes conditioned by the lack of an economical standardization of reported costs. A study from 2014 reported that robotic-assisted colorectal resections had higher total ($5,272 increase, *p* < 0.001) and direct costs ($4,432 increase, *p* < 0.001), longer operating time (39 min, *p* < 0.001), and were more frequently associated to postoperative bleeding (OR 1.6, *p* = 0.014) than laparoscopic resections. The data source for this study was a United States national inpatient database evaluating a total of 17,265 laparoscopic and 744 robotic colorectal resections between 2009 and 2011 (10). However, there were some limitations in this study that may have influenced the results. First, the authors used an administrative database which had the possibility of coding errors. Second, many centers were involved, which also suggests a high heterogeneity of the techniques in both the laparoscopic and robotic groups, including the type of devices, the implementation of hybrid vs. totally robotic techniques, the phase of the learning curve, and patient volume at the center. Furthermore, some data were missing, such as the conversion rate.

The main reasons why the costs of robotic approach are poorly reported in the literature are mainly due to the challenge in their calculation. If, from one hand, costs associated with the hardware are easy to obtain, the impact of the surgical procedure on overall costs is difficult to be quantified.

Indeed, overall costs should include not only operative costs but also costs related to the rehabilitation facility, days out of work after surgery and its impact on the quality of life (QoL), which make an exact estimate challenging. Studies which address the impact of costs of a new technique on QoL are named *cost-effectiveness studies*.

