## The Rationale for the Study

The current debate about introducing a new technology mainly concerns its cost-effectiveness (15). Only a cost-effectiveness analysis can shed light on uncertainties concerning the economic impact of robotic vs. laparoscopic surgery. However, reliable, prospective, adequately designed cost-effectiveness studies are still lacking (16–21).

QoL after a surgical procedure can be measured through different scores (22). In order to conduct cost-effectiveness studies, QoL needs to be objectively and consistently measured, using validated tools. The most used scores to grade QoL are the generic SF-36 and the EuroQol EQ-5D-5L tests, that can be transformed into QALYs, giving a more objective view of the patient's improvement after the planned treatment (health perspective) (23).

Apart from prospective series, some studies only used a decision-analytic model derived from available literature for costs, QoL and outcomes (24). However, these results must be interpreted with great caution since the insufficient data available in the literature imply a high risk of bias.

According to the pyramid of evidence, randomized clinical trials represent the highest level of study types. However, in a surgical setting of robotic vs. laparoscopic approach, these trials are difficult to be performed (e.g., expensive, ethical issue, blinding) and generalized (strict inclusion criteria) (25). Hence, prospective, adequately designed and conducted non-randomized clinical trials can provide very clinically relevant information.

A well-designed cost-effectiveness study would answer whether its superiority justifies the higher costs of robotics in terms of gained QoL after surgery. This protocol describes the study of nationwide assessment of the cost-effectiveness of the laparoscopic vs. robotic approach, which will define which approach is more convenient for each condition or patient.

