## Aims of the Study

### Primary Aim of the Study

To determine if robotic surgery is more cost-effective than laparoscopic surgery in several surgical conditions and patient populations. The present prospective study will evaluate the incremental cost per quality-adjusted life year (QALY) gained from healthcare perspectives.

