### Cost-Effectiveness Analysis

The economic evaluation will be performed as cost effectiveness and cost–utility analyses from a healthcare perspective, with a time horizon of 3 months.

The cost–utility endpoint will be the cost per QALY. The results will be reported in accordance with CHEERS guidelines (23). Data will be collected in the early post-operative period of time (3 months from the surgery) in order to capture as much as possible only the QoL mainly related to the surgical approach instead of the issues related to all treatment process (adjuvant treatment, stoma issues, etc.) which patients are dealing with in a later period of time.

An independent company (Institute for Validation of Clinical Efficacy - IVEC) will perform the financial analysis, eliminating the risk of an observer bias.

A model-based cost-utility analysis estimating mean costs and QALYs per patient will be performed. A stochastic cost-utility analysis will be undertaken. The incremental cost-effectiveness ratio (ICER) will be estimated using the overall costs of the robotic and laparoscopic procedures and QALYs derived from patient interviews to find the incremental cost per QALYs gained.

The INB will be calculated to estimate decision-makers maximum willingness to pay (WTP) for a QALY gained. The INB will be calculated as the mean QALYs per patient multiplied by WTP threshold minus the mean cost per patient for the treatment. The decision rule is to adopt the treatment if the INB > 0, and the alternative with the highest INB represents best value for money.

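### Robot acquisition and maintenance are left out of the costs without a stated reason, so a positive INB does not support the unrestricted cost-effectiveness aim (an INB at or below zero still stands)

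*Protocol article*

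**What the plan says.** The article poses a broad question. Its primary aim is: "To determine if robotic surgery is more cost-effective than laparoscopic surgery in several surgical conditions and patient populations". The measure is the "incremental cost per quality-adjusted life year (QALY) gained from healthcare perspectives". The rationale frames the purpose in the same way: "A well-designed cost-effectiveness study would answer whether its superiority justifies the higher costs of robotics in terms of gained QoL after surgery". None of these statements is limited to hospitals that already own a robot.

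On the reasons robotic surgery costs more, Current Evidence says: "Contributing factors include purchasing the robot by the healthcare institution, maintenance costs, disposable materials, and longer operative times". The same section remarks that "costs associated with the hardware are easy to obtain".

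The Cost Data section then sets the cost base: "Overall direct hospital costs will be collected, except for the costs associated with the acquisition or maintenance of the robotic device". No reason follows. The next exclusion in that section does carry one: "Pre-admission charges for screening will not be considered, as these are equal for both surgical techniques".

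In Cost-Effectiveness Analysis, the ICER "will be estimated using the overall costs of the robotic and laparoscopic procedures", and the treatment is to be adopted when the INB is above zero. WTP is set at 20,000 and 30,000 EUR per QALY and the time horizon is 3 months.

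**The concern.** The two excluded items are the first two that the article itself lists as drivers of robotic cost. They fall on one arm only, so the omission can move the comparison in one direction only. The reason given for dropping screening charges, equality between techniques, cannot apply to a device used in one arm. The remark on hardware costs also removes an obvious feasibility reason.

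What is at stake is the primary conclusion. A positive INB triggers the adoption rule and would be reported as robotic surgery being cost-effective from a healthcare perspective. Yet the whole of that positive value could be the cost that was left out. A larger sample would not help, because this is a shift in the quantity being estimated and not sampling error.

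**Working it through.** **Inputs from the article.** INB formula (Sample Size): effect difference times WTP, minus cost difference. WTP: 20,000 and 30,000 EUR per QALY. Horizon: 3 months = 0.25 year. Discount rate: 3% per year (Cost Data). The article gives no robot price, maintenance charge, device lifetime or caseload, so the per-case cost c is unknown.

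**The article's own computed figure.** The only one is 30 patients per arm. It cannot be reproduced, because no standard deviation is given, and this point does not rest on it.

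**Step 1: direction and size of the shift.** Let c be the omitted acquisition plus maintenance cost per robotic case, in EUR, and ΔC the cost difference as the plan would measure it.

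- Plan as written: INB(excl) = ΔQALY × WTP − ΔC
- With the omitted items: INB(full) = ΔQALY × WTP − (ΔC + c) = INB(excl) − c

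The shift is exactly c and does not depend on WTP. Cost-Effectiveness Analysis also describes INB per treatment, as mean QALYs times WTP minus mean cost. On that definition the robotic value rises by c and the laparoscopic value does not, so the comparison moves by the same c.

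**Step 2: which results survive.**

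- INB(excl) ≤ 0 implies INB(full) ≤ −c < 0. A negative finding holds.
- INB(excl) > 0 leaves the sign of INB(full) open. It is positive only if c < INB(excl).
- For the acceptability curve, the plan estimates the probability that INB(excl) > 0, while the unrestricted aim needs the probability that INB(excl) > c. The first can never be the smaller.

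**Step 3: QALY gain needed to offset c.** The gain needed is c / WTP. Dividing by 0.25 gives the utility difference that must hold for all 3 months. The values of c are illustrative.

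| c (EUR per case) | QALY at 20,000 | QALY at 30,000 | Utility difference at 20,000 | Utility difference at 30,000 |
|---|---|---|---|---|
| 500 | 0.025 | 0.017 | 0.10 | 0.07 |
| 1,000 | 0.050 | 0.033 | 0.20 | 0.13 |
| 2,000 | 0.100 | 0.067 | 0.40 | 0.27 |
| 3,000 | 0.150 | 0.100 | 0.60 | 0.40 |

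If utilities are taken to lie between 0 and 1 (an assumption; the article names no value set), the most a patient can gain in 3 months is 0.25 QALY. That is worth 0.25 × 20,000 = 5,000 EUR or 0.25 × 30,000 = 7,500 EUR. At c = 1,000 EUR and the lower threshold, the offset takes 0.05 / 0.25 = 20% of that ceiling.

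**Step 4: a range for c, wholly assumed.** c = (price × annuity factor + yearly maintenance) / yearly caseload, with annuity factor 0.03 / (1 − 1.03^−life).

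- Low: price 1.0 million EUR, maintenance 100,000 EUR, 10 years, 400 cases. Factor 0.1172; (117,231 + 100,000) / 400 = 543 EUR.
- Middle: price 1.5 million EUR, maintenance 150,000 EUR, 10 years, 200 cases: 1,629 EUR.
- High: price 2.0 million EUR, maintenance 200,000 EUR, 7 years, 100 cases. Factor 0.1605; (321,013 + 200,000) / 100 = 5,210 EUR.

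None of these inputs comes from the article. The spread shows how strongly c depends on caseload and lifetime.

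**Step 5: effect on sample size.** Adding a constant to every robotic case moves the mean cost and leaves its variance unchanged, so the required number is the same.

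**The case against.** The strongest defence is that the exclusion is openly stated and amounts to a running-cost perspective. For a hospital that has already bought a robot, the purchase is sunk, and leaving it out is a defensible choice. This stands as a description of a narrower question. It does not rescue the stated aim, which is never narrowed in that way, and maintenance is a recurring cost that cannot be called sunk.

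Several further points limit what can be claimed:

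- **The study cannot answer its question.** A reader might infer this, but Step 2 shows otherwise: an INB at or below zero stands. Adding the same c to every procedure would also leave the ranking of procedures by INB unchanged, although not which of them exceed zero.
- **The sections contradict each other.** The cost total named in Cost-Effectiveness Analysis can be read as the quantity that Cost Data has just defined, exclusion included. The mismatch is one of scope and wording, not of two opposing rules.
- **Laparoscopic equipment is treated differently.** Costs come from the RECH database, and the article does not say whether its per-patient costs include depreciation of laparoscopic equipment. Unequal treatment is possible but not shown.
- **No scenario restores the costs.** None is described, but a condensed article may leave scenario lists to the full plan, so that absence is not itself a fault. The tornado diagram names total robotic cost as an input. Nothing says its range covers capital or maintenance, so this helps only in part.
- **The omitted cost matches the 3,000 EUR in the sample size section.** That figure is a ratio per QALY gained; c is a cost per case. The two cannot be compared.

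**Conclusion.** The point holds in a limited form. The base case leaves out, without a reason, two cost items that the article itself counts among the drivers of higher robotic cost. The aim and the adoption rule carry no matching restriction. The direction is certain: the omission favours robotic surgery by exactly c EUR per case at either threshold. A positive INB therefore supports only a statement about costs excluding acquisition and maintenance of the robot, while an INB at or below zero needs no such qualification.

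The size is not certain, because the documents give no value for c and any euro figure is an assumption. The illustration of 1,000 EUR shows that even a moderate amount would require a sizeable quality-of-life advantage within so short a horizon. The conclusion rests on the protocol's INB formula and on c being positive, not on any particular value of c.

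**What to change.** 1. In Cost Data and Cost-Effectiveness Analysis, pre-specify an analysis that adds an annualised acquisition plus maintenance cost to each robotic case. Use a 3% annuity and divide by the robot's total yearly caseload across all users. Carry this through Sensitivity Analysis and Acceptability Curve, with caseload and device lifetime varied.
2. Establish whether RECH costs include laparoscopic equipment, and treat both techniques alike.
3. Apply the INB > 0 rule to the unrestricted aim only on the full-cost result. Whether full cost is labelled the base case or a pre-specified companion analysis is open to debate; tying the rule to it is what matters.
4. Where a centre cannot supply figures, report the break-even capital cost per case. By Step 1 this equals the INB without capital, at each of the two thresholds. Word the aim, decision rule and conclusion as *excluding acquisition and maintenance of the robot*.

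The cost is a few fields per centre (price, maintenance contract, lifetime, yearly caseload) and one more model input. Surgical volumes are already requested at registration, but the article does not say that they include other specialties sharing the robot, so that field would need checking. These are centre-level inputs that can be added at analysis, so no patient data are lost. The required sample size is unchanged if a constant per-case cost is added. The full-cost result will be less favourable to robotic surgery.

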## Auditing

Independent qualified monitors will monitor the study. Data will be entered into an electronic eCRF, and after the monitoring, visits will be marked as “complete data.” Monitoring visits will be scheduled according to the number of visits ready for verification. The date of the visit will be agreed upon with centers in advance. Before initiation of the trial, interactive training will be conducted, and an electronic test database will be created for familiarization with the system and test data entry. Data's completeness, validity, and plausibility will be checked at the time of data entry (edit checks) and by using validating programs that generate queries. The completed eCRF must be reviewed and signed by the investigator named in the trial protocol or a designated sub-investigator. The investigator or the designated representative will be obliged to complete the eCRF as soon as possible after information is collected and to clarify or explain the queries.

## Sample Size Calculation and Statistical Methods

### Sample Size

There are concerns about calculating power and sample size in cost-effectiveness studies (28). Although there is some uncertainty, the Incremental Net Benefit (INB) is a measure that is easier to interpret and work with, since a positive INB means that the new proposed treatment is cost-effective (29). Medicare calculations of power and sample size are calculated against some value of Maximum Willingness to Pay (WTP) for a unit of treatment effect. The WTP is defined from a societal perspective, and, although in Spain there is no specific WTP threshold in healthcare, according to the National Institute for Health Care Excellence (NICE) (30) and Spanish Recommendations on Economic Evaluation of Health Technologies (31) we use a WTP of 20,000 € and 30,000 € per QALY as a threshold, to recognize which treatment is most cost-effective, as follow:

$$\begin{array}{l} \text{INB}=\left[\left(\text{EffectNew-EffectComparatore}\right)*\text{WTP}\right]\\ -\left(\text{CostNew-CostComparator}\right) \end{array}$$

This sample size calculation was realized with consultation of two statisticians.

Considering previous retrospective reports on cost-effectiveness studies (16–21) in which a minimum of 3,000 € for QALY gained was considered cost-effective, assuming a 5% lost-to-follow-up-rate and the two-sided significance level (α) set at 5% and power (1-β) at 80%, a minimum total of 60 patients need to be allocated in each procedure group comparison (30 laparoscopic vs. 30 robotic).

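### The 80% power claimed for 30 versus 30 in every procedure rests on a cost-per-QALY ratio, which fixes no net-benefit difference to be powered for

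*Protocol article*

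**What the plan says.** The Sample Size section of the protocol article introduces INB as the easier measure to work with and gives its formula: the effect difference times willingness to pay (WTP), minus the cost difference. It then sets the thresholds: "we use a WTP of 20,000 € and 30,000 € per QALY as a threshold". The calculation itself follows in one sentence. It opens "Considering previous retrospective reports on cost-effectiveness studies", takes from those reports the effect "in which a minimum of 3,000 € for QALY gained was considered cost-effective", adds "assuming a 5% lost-to-follow-up-rate", a two-sided 5% significance level and 80% power, and concludes that "a minimum total of 60 patients need to be allocated in each procedure group comparison (30 laparoscopic vs. 30 robotic").

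The Study Population section lists seven operations, from inguinal hernioplasty to distal pancreatectomy and rectal cancer resection. The same size applies to each. The Cost-Effectiveness Analysis section sets the evaluation "from a healthcare perspective, with a time horizon of 3 months". The article gives no target INB difference, no cost or QALY difference and no SD, and it does not say which of the two WTP values entered the calculation.

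**The concern.** A two-group calculation for mean INB needs a difference in euros and an SD in euros. A figure in euros per QALY is a different kind of quantity. By the article's own formula it becomes an INB only once the QALY gain and the WTP are known. The ratio also lies far below the thresholds by which the study will judge cost-effectiveness, and nothing in the section explains how the two relate.

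The study aims to say which approach is more cost-effective, procedure by procedure. If readers take 80% power as established for each comparison, an INB whose interval includes zero could be taken as evidence of no difference, when the comparison may have had little chance of showing one.

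**Working it through.** **Inputs from the article:** two-sided α 0.05; power 0.80; loss 5%; 30 per arm; WTP 20,000 and 30,000 €/QALY; horizon 3 months (0.25 year); effect figure 3,000 € per QALY gained. **Not in the article:** the SD of INB, the QALY difference and the cost difference. SDs and QALY gains below are assumptions unless marked as back-solved.

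**1. Can the stated size be reproduced?** Not from the stated inputs. It can only be solved backwards. Take 3,000 € as a mean INB difference Δ and use n = 2(1.960 + 0.842)² × SD²/Δ². An SD of 4,000 € gives 15.70 × (4,000/3,000)² = 27.9, so 28 per arm, and 28/0.95 = 29.5, so 30. The stated size matches a 3,000 € difference with an SD near 4,000 €, but that SD is inferred and not a document input.

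**2. What 30 per arm delivers.** After 5% loss, 30 × 0.95 = 28.5 remain. With the t distribution, 80% power needs a standardised difference of 0.755 at 28.5 per arm and 0.762 at 28. For 3,000 € the SD may then be at most 3,000/0.755 = about 3,970 €, or 3,000/0.762 = about 3,935 €; call it 3,950 €. The 95% CI half-width is 2.00 × √(2/28.5) = 0.53 SD.

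**3. Reading A: an INB difference of 3,000 €, in either direction** (28 evaluable per arm, t-test).

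| Assumed INB SD (€) | Power |
|---|---|
| 3,000 | 96% |
| 4,000 | 79% |
| 5,000 | 60% |
| 6,000 | 45% |
| 8,000 | 28% |
| 10,000 | 20% |

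If costs were equal, 3,000 € would need 3,000/30,000 = 0.10 QALY or 3,000/20,000 = 0.15 QALY. Over 0.25 year that is a mean utility gap of 0.10/0.25 = 0.40 or 0.15/0.25 = 0.60.

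**4. Reading B: an ICER of 3,000 €/QALY.** The cost difference is then 3,000 × ΔQALY, so INB = ΔQALY × (WTP − 3,000).

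- Assumed gain of 0.02 QALY (mean utility gap 0.02/0.25 = 0.08): 0.02 × 17,000 = 340 €, or 0.02 × 27,000 = 540 €. Power at an assumed SD of 3,000 € is about 7% and 10%.
- Assumed gain of 0.05 QALY (utility gap 0.20): 850 € or 1,350 €. At an assumed SD of 4,000 € this needs about 348 or 138 per arm before loss.

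The two readings give targets that can differ several-fold, and the text does not say which was meant.

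**The case against.** Several points on the other side are sound.

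- **The horizon.** A reader might infer that 3,000 € cannot arise within 3 months. That is not supported. A ratio of 3,000 €/QALY can arise over any horizon (30 € for 0.01 QALY). With utilities between 0 and 1, up to 0.25 QALY can accrue, worth 5,000 € or 7,500 € at the two thresholds, so an INB of 3,000 € lies below the ceiling. A utility gap of 0.40 to 0.60 is very large but not impossible.
- **Costs count too.** INB includes the cost difference and the test is two-sided, so an excess robotic cost is as much a target as a benefit. The Current Evidence section cites a total-cost excess of $5,272 for robotic colorectal resection, and also reports possible savings on hospital stay. The Cost Data section leaves out acquisition and maintenance of the robot.
- **The number itself.** A reader might infer that most of the procedures are underpowered. The article has no SD on which to base that; at an SD of 3,000 € power would be 96%. Step 1 shows that 30 may be the right result of a badly worded calculation.
- **A condensed article.** The SD and derivation may be in the full protocol, and two statisticians were consulted. The missing SD alone would not be a finding.
- **Attribution.** The 3,000 € figure is credited to earlier reports. The study's own thresholds are 20,000 and 30,000 €/QALY throughout.
- **Reporting.** The decision rule is INB above zero, with simulation-based 95% intervals and an acceptability curve. Nothing says that a non-significant result will be reported as no difference.

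These points narrow the concern but do not remove it. Condensation explains an absent SD. It does not explain an effect in the wrong units, printed as the basis for the size and left unreconciled with the thresholds beside it.

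**Conclusion.** Wrong as written, and it should be fixed. The stated effect is a ratio and determines no INB difference, so the blanket 80% power does not follow from the inputs given.

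If a 3,000 € INB difference was meant, the claim is conditional on an INB SD of about 3,950 € or less in each of seven quite different operations. If an ICER was meant, the INB is a few hundred euros for small QALY gains, and 30 per arm falls far short at the SDs tried for such gains. The threshold of 0.76 SD and the half-width of 0.53 SD depend only on α, power, the arm size and the loss rate, under a two-sample t-test with equal variances. The powers by SD are illustrative. What is established is that 80% power is not shown, not that it is absent or that 30 per arm is the wrong number.

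**What to change.** In the Sample Size section:

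1. Replace the ratio with a target difference in mean INB, in euros, at one named WTP. Give its SD and the source of that SD.
2. Replace the blanket 80% with what 30 per arm (about 28 evaluable) delivers in each procedure: about 80% power for INB differences of 0.76 SD or more, and a 95% CI half-width of about 0.53 SD. Express both in euros where a procedure-specific SD is available.
3. State that each procedure will be reported by its INB with CI, and that a non-significant result will not be read as no difference. This extends the interval reporting already planned.

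The cost is a wording change, and the stated power may become less favourable. The restatement itself needs no extra patients. If the sponsor instead wishes to keep 80% power for a stated euro difference, the size must be recalculated per procedure and could rise. For a 3,000 € difference, an assumed SD of 5,000 € would need 47 per arm including loss.
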